### Sample size justification

Assuming a gender specific effect of a physical activity intervention, the statistical power had to be strong enough to allow separate analyses for girls and boys. A group difference of 0.6 standard deviations after intervention might be relevant for preventive reasons. With an usual main level of significance α = 0.025 (two primary outcomes) and β = 0.80 power, a minimum of 53 persons per group have to be available for analysis in a non-clustered design. To account for possible missing data from both follow-up visits during the intervention period due to non-participation in both tests or due to drop-out - estimated to occur in about 5% of the participating children - sample size has to be adjusted accordingly. Since accelerometry was required for one of the primary outcomes and accelerometry data are often too incomplete for valid analysis, sample size was further increased by 20%.

Because of cluster sampling (randomisation of children into intervention or control group according to the child's kindergarten) the number of subjects needed was increased by another 30% in the initial sample size calculation. In order to meet current standards of power calculation in cluster randomised trials we performed an additional calculation considering intraclass correlation. Assuming an intraclass correlation of ρ = 0.1 [18] and an average cluster size of 17 children per kindergarten, the sample size had to be increased by 160% [19].

Thus, a total of 174 girls and 174 boys were required for the intervention group and the same numbers of boys and girls for the control group.

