### Data analysis

A composite motor skills score will be calculated by averaging the z-transformed results of the obstacle course, the standing long jump, the balancing on one foot task, and the jumping to and fro sidewise task to describe the baseline situation. Likewise, the changes in performance from baseline of the above motor skills tests will be z-transformed and averaged for each of the three follow-up time points. For these computations, the values of the obstacle course and the balancing task will be multiplied by "-1" to account for the fact that a low score in these tasks indicates a better performance.

Baseline data will be explored by descriptive statistics. Differences between the intervention and the control group at baseline will be analysed by two sample Students t-tests for normal distributed interval scaled variables, by Wilcoxon Tests ordinal and/or not normal distributed variables and by Chi-squared statistics for nominal variables.

The primary endpoints will be analysed by a repeated measurement analysis of covariance with the changes form baseline to the two assessments during the intervention period as dependent variables and including the fixed factors intervention, gender, and urban/rural location of the kindergarten, the random factor kindergarten and the covariate age in the model. For the composite score, the mean of the z-scores of the changes in performance and the mean of the z-scores of the baseline values are used respectively. The same statistical procedure will be used for the secondary outcome variables in an exploratory manner. Predefined gender specific subgroup analyses will be performed. Several additional explorative analyses will also be performed concerning the intervention effects on selected primary and secondary outcomes in specific subgroups, such as children with different body composition, children with low motor skills performance at baseline, children with low socioeconomic status and or with a migrant status, respectively.

As effects of the intervention are anticipated to become apparent in the entire distribution of motor skills scores, no specific threshold is presumed.

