There are two primary endpoints, namely the change in moderate-and-vigorous physical activity and the composite score of changes in motor skills during the intervention period. Therefore, the Bonferroni adjusted 2 sided significance levels of 0.025 are used for the analysis of primary endpoints. For all secondary endpoints, statistical significance will be considered at p < 0.05.

Effects will be analysed primarily as intention-to-treat-analyses and additionally as per-protocol analyses.

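### The sample size assumes a gender-specific effect, but the listed model has no intervention-by-gender term and the separate subgroup analyses do not test whether the effect differs by sex

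*Protocol article*

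**What the plan says.** All references are to the protocol article.

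- **Sample size justification.** The premise is "Assuming a gender specific effect of a physical activity intervention", and the consequence drawn is that "the statistical power had to be strong enough to allow separate analyses for girls and boys". The target is 0.6 SD: "A group difference of 0.6 standard deviations after intervention might be relevant for preventive reasons". Error rates are given as "With an usual main level of significance α = 0.025 (two primary outcomes) and β = 0.80 power" (read here as 80% power), which leads to "a minimum of 53 persons per group have to be available for analysis in a non-clustered design". After inflation, 174 girls and 174 boys are required in each arm.
- **Data analysis, primary model.** This is a repeated-measures analysis of covariance of the two changes from baseline, "including the fixed factors intervention, gender, and urban/rural location of the kindergarten", with kindergarten as a random factor and age as a covariate. No intervention-by-gender term is named.
- **Data analysis, sex.** The sex question is taken up in one sentence: "Predefined gender specific subgroup analyses will be performed".
- **Data analysis, significance level.** For the two primary endpoints, "the Bonferroni adjusted 2 sided significance levels of 0.025 are used for the analysis of primary endpoints".

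**The concern.** The premise behind the sample size is that the intervention may act differently in girls and boys. The method given for that question is an analysis within each sex. Such analyses answer whether there is an effect in girls and whether there is one in boys. They do not answer whether the two effects differ, because one significant and one non-significant result can easily come from the same underlying effect.

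At stake is the interpretation of the sex-specific results. A reader who sees significance in one sex only will tend to conclude that the programme works in that sex and not in the other. Without a prespecified estimate of the difference, the report would have no planned result to set against that conclusion. The Discussion foresees nationwide transfer if the trial succeeds, so a misleading message of this kind could travel with the programme.

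**Working it through.** **1. Reproducing the plan's figures.** Inputs from Sample size justification and Data analysis: 0.6 SD, two-sided alpha 0.025, power 0.80, 5% missing, a further 20% for accelerometry, intraclass correlation (ICC) 0.1, 17 children per kindergarten.

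- Unclustered n per group = 2 × (2.241 + 0.842)² / 0.6² = 52.8, so 53.
- Design effect = 1 + (17 − 1) × 0.1 = 2.6, the stated 160% increase.
- 53 × 1.05 × 1.20 × 2.6 = 173.6, so 174 per sex per arm.

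Both figures reproduce. The power statement therefore applies within each sex.

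**2. Discordant results at the stated power.** Suppose the true effect is equal in both sexes and each sex-specific test has power p. If the tests are independent,

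P(exactly one significant) = 2p(1 − p) = 2 × 0.80 × 0.20 = 32% per endpoint.

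Girls and boys share kindergartens, so the two estimates are positively correlated. Then P = 2 × (p − P(both significant)), with P(both) from a bivariate normal distribution:

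| Correlation | 0 | 0.2 | 0.4 | 0.6 |
|---|---|---|---|---|
| Exactly one significant, p = 0.80 | 32% | 29% | 25% | 20% |

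**3. Discordant results with the kindergartens modelled.** Assumptions: 174 × 0.80 = about 139 usable children per sex per arm; 41 / 2 = 20.5 kindergartens per arm; so m = 139 / 20.5 = 6.78 children of one sex per kindergarten; ICC 0.1, shared by both sexes.

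- Variance of one sex-specific effect = (2 / 20.5) × (0.1 + 0.9 / 6.78) = 0.0227; SE = 0.151 SD.
- Correlation between the two sex-specific estimates = 0.1 / (0.1 + 0.9 / 6.78) = 0.43.
- Power at 0.6 SD = Φ(0.6 / 0.151 − 2.241) = 96%.

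| True effect, both sexes | Power per sex | Exactly one significant | Range, ICC 0.01 to 0.15 |
|---|---|---|---|
| 0.3 SD | 40% | 35% | 29–47% |
| 0.4 SD | 66% | 33% | 26–33% |
| 0.5 SD | 86% | 19% | 7–22% |
| 0.6 SD | 96% | 7% | 1–11% |

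Power at 0.6 SD exceeds the planned 80% because the design effect of 2.6 uses all 17 children in a kindergarten. A one-sex analysis has about 8.5, giving 1 + 7.5 × 0.1 = 1.75.

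**4. What an interaction test would offer.** Under the same assumptions, and with no sex-by-kindergarten variance, the shared kindergarten effect cancels from the girl–boy contrast:

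- Variance = (4 / 20.5) × (0.9 / 6.78) = 0.0259; SE = 0.161 SD.
- Power at alpha 0.025 for a difference of 0.6 SD = Φ(0.6 / 0.161 − 2.241) = 93%.
- For a difference of 0.3 SD = Φ(0.3 / 0.161 − 2.241) = about 35%.

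If the effects are equal, this test declares a sex difference only at its nominal rate.

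**The case against.** **Separate analyses are a legitimate aim.** Wanting enough power to detect 0.6 SD within each sex is a sound objective, and separate analyses serve it. That stands. A reader might infer that the plan will claim a sex difference from one significant and one non-significant result. The text states no such rule, so the risk lies in how the results will be read.

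**The model description is condensed.** It lists factors without saying that these are main effects only, and it names no time factor although the model has repeated measurements. A fuller analysis plan might contain the interaction. This limits the point to what the article states. But the article does more than stay silent: it makes a gender-specific effect the premise of the sizing and names subgroup analyses as the way of handling it.

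**Multiplicity.** A reader might infer that testing two sexes on two endpoints at 0.025 inflates the trial's overall error. The documents do not support that. The Bonferroni split covers the two primary endpoints, no sex-specific result is listed as a primary or secondary outcome, and the sex-specific work is labelled subgroup analysis. No stated confirmatory claim carries the extra error.

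**Ability to show a difference.** A reader might also infer that the trial could not demonstrate a true sex difference. That is not so. The data would support an interaction test, with good power for a large difference. What is absent is the prespecification.

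**Size.** The 32% needs independence and exactly 80% power. With shared kindergartens and the required sample, the chance at the full 0.6 SD is only about 7%. This stands, and it limits the concern mainly to true effects below the target.

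**Conclusion.** The point holds as a mismatch between the sizing premise and the stated analysis: the sample size rests on an assumed gender-specific effect, while no listed term or test addresses whether the effect differs by sex.

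With equal true effects, a result significant in exactly one sex would arise in about 20–32% of trials per endpoint at the nominal 80% power per sex. With clustering modelled, it would arise in about a third of trials at 0.3 to 0.4 SD, falling to 19% at 0.5 SD and 7% at 0.6 SD. The clustered figures rest on assumed values for usable children and kindergartens per arm, on the plan's ICC of 0.1, and on normal approximations.

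The pooled intervention effect, which is the primary analysis, is untouched. The change is worth making because it costs little and settles in advance how sex-specific results may be described.

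**What to change.** - Add intervention × gender to the same mixed model, as a prespecified secondary, non-confirmatory test for each primary endpoint.
- Report girls' and boys' effects with confidence intervals as contrasts from that model, in place of two separate significance verdicts.
- State that any claim of a sex difference will rest on the interaction estimate and its confidence interval, and that the pooled intervention effect remains the confirmatory test.

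The cost is one model term and a sentence or two of text, with no change to the sample size or the alpha split. The drawback is limited power for small differences: about 35% for 0.3 SD against 93% for 0.6 SD at alpha 0.025, and less if the sex difference itself varies between kindergartens. A non-significant interaction should therefore be reported with its interval and not as evidence that the effects are equal.

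### Fixed Bonferroni at 0.025 for the two primary endpoints is valid, but Holm's step-down would give some power at the same family-wise error

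*Protocol article*

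**What the plan says.** Under Data analysis, the protocol article sets out the primary family: "There are two primary endpoints, namely the change in moderate-and-vigorous physical activity and the composite score of changes in motor skills during the intervention period". It then fixes the threshold: "the Bonferroni adjusted 2 sided significance levels of 0.025 are used for the analysis of primary endpoints". Each endpoint is judged at 0.025 whatever the other shows, and no step-down rule is mentioned. Secondary endpoints are judged at 0.05 in an exploratory manner.

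Sample size justification uses the same level for the same reason: "With an usual main level of significance α = 0.025 (two primary outcomes) and β = 0.80 power" (the 0.80 is plainly the power). The target effect is introduced with "A group difference of 0.6 standard deviations after intervention might be relevant for preventive reasons", and the result is that "a minimum of 53 persons per group have to be available for analysis in a non-clustered design". That number applies to each gender, because "the statistical power had to be strong enough to allow separate analyses for girls and boys". The primary model under Data analysis, however, pools girls and boys with gender as a fixed factor. The gender-specific analyses are named there as predefined subgroup analyses.

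**The concern.** Under fixed Bonferroni, success on one endpoint never relaxes the threshold for the other. Suppose motor skills succeed at 0.025 and MVPA (moderate-and-vigorous physical activity) gives p = 0.03. MVPA is then not significant, although the 5% family-wise budget would allow that claim under Holm. MVPA at the 2-4 month follow-up, a secondary outcome, would be called significant at the same p = 0.03.

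The loss falls mainly on the chance of showing both effects. That matters here because the Discussion section of the Abstract ties nationwide distribution to effectiveness on activity levels and on motor skills.

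**Working it through.** **Inputs from the article.** Two primary endpoints; two-sided 0.025 each; power 0.80; difference 0.6 SD; missing data "estimated to occur in about 5% of the participating children"; a further 20% for accelerometry; intraclass correlation 0.1 with 17 children per kindergarten; 174 per gender per arm.

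**Assumed, not in the article.** The correlation between the two primary test statistics (0 to 0.8), and the same 0.6 SD effect on both endpoints.

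**1. The plan's own figures reproduce.**
- n per group = 2(2.2414 + 0.8416)² / 0.6² = 52.8, so 53. (This is the normal approximation; the noncentral t gives power 0.791 at 53.)
- Design effect = 1 + 16 × 0.1 = 2.6, and 53 × 1.05 × 1.20 × 2.6 = 173.6, so 174.
- Total alpha = 2 × 0.025 = 0.05.

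**2. Holm keeps the same family-wise error.**
- If both null hypotheses are true, a false rejection needs the smaller p to be at most 0.025. The probability is at most 0.025 + 0.025 = 0.05.
- If one is true, a false rejection needs that p to be at most 0.05, so the probability is again at most 0.05.
- Neither step uses the correlation.
- In simulation with both nulls true, family-wise error is the same for both methods: 0.049 at correlation 0 and 0.040 at 0.8.
- With one null true and 0.6 SD on the other endpoint (53 per group), Holm falsely rejects the true null in 0.045 (correlation 0) to 0.039 (0.8) of trials, against 0.025 for Bonferroni. Holm uses more of the 5% but does not exceed it.

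**3. Power at 53 per group, independent endpoints.**
- Noncentrality = 0.6 × √(53/2) = 3.0887.
- Power at 0.025 = Φ(3.0887 − 2.2414) = 0.802; at 0.05 = Φ(3.0887 − 1.9600) = 0.870.
- Holm per endpoint = 0.802 + (0.870 − 0.802) × 0.802 = 0.857.
- Both endpoints: Bonferroni 0.802² = 0.643; Holm 0.870² − (0.870 − 0.802)² = 0.752, or 0.753 without rounding.

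**4. Across the assumed correlations** (bivariate normal simulation, 2 million draws per setting; Bonferroni → Holm). The pooled effective size is 2 × 53 = 106 per arm; equivalently 2 × 174 / (1.05 × 1.20 × 2.6) = 106.

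| Effective n per arm | Correlation | Per endpoint | Both | At least one |
|---|---|---|---|---|
| 53 (one gender) | 0 | 0.802 → 0.857 | 0.643 → 0.754 | 0.961, unchanged |
| 53 | 0.5 | 0.802 → 0.847 | 0.689 → 0.780 | 0.914, unchanged |
| 53 | 0.8 | 0.802 → 0.839 | 0.731 → 0.806 | 0.872, unchanged |
| 106 (pooled) | 0 | 0.983 → 0.992 | 0.967 → 0.984 | above 0.999, unchanged |
| 106 | 0.5 | 0.983 → 0.991 | 0.969 → 0.984 | 0.997, unchanged |
| 106 | 0.8 | 0.983 → 0.989 | 0.974 → 0.986 | 0.993, unchanged |

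**5. When the pooled analysis would see the larger gain.** Pooled power at 0.025 is 80% when the effect is 0.6/√2 = 0.42 SD, because 0.42 × √(106/2) gives about the same noncentrality of 3.09. The rows for 53 then apply to the pooled test.

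**The case against.** The strongest objection is that nothing is wrong. Bonferroni at 0.025 controls family-wise error, is prespecified, agrees with the sample size section and gives simple matching 97.5% intervals. A more powerful procedure does not turn a valid one into an error. This stands, and the point is one of efficiency only.

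Second, a reader might infer that the main analysis would gain 6 points per endpoint and 11 for both. The article does not support that. Those figures belong to the gender-specific size and to independent endpoints, the most favourable case. The primary model pools the genders, and at 0.6 SD it has little left to gain.

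Third, the 20% allowance is for accelerometry alone, so motor skills should have more usable data: 53 × 1.20 = 63.6 per group and power Φ(0.6 × √(63.6/2) − 2.2414) = 0.873. Equal power is therefore a simplification. It changes little. With power at 0.05 of 0.923 for motor skills and independent endpoints, power for both goes from 0.802 × 0.873 = 0.70 to 0.870 × 0.923 − (0.870 − 0.802)(0.923 − 0.873) = 0.80.

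Fourth, a reader might take the endpoints as co-primary in the strict sense, with both required. The analysis section does not say so. If both were required, each could be tested at 0.05 and neither correction would be needed.

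Fifth, Assessments dates the last measurements to September-November 2008 and describes them in the past tense. Relaxing a threshold after data collection invites doubt. The article still describes the analysis as planned, but it does not show whether primary results had been seen.

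**Conclusion.** This is an optional improvement, not an error or a contradiction. Holm never rejects less than the planned rule and holds the same 5% family-wise error. It adds nothing to the chance of at least one significant primary endpoint.

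At the gender-specific size the gain is about 4-6 points per endpoint and 7-11 points for both. In the pooled primary analysis at 0.6 SD it is about 1 point per endpoint (0.983 to 0.989-0.992) and 1-2 points for both (0.967-0.974 to 0.984-0.986). The larger figures apply there only if the true pooled effect is near 0.42 SD.

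All of this rests on the assumed correlation range of 0 to 0.8 and on equal effects on both endpoints. It gives no ground for reducing the sample size, because Holm's first step still uses 0.025.

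**What to change.** Under Data analysis, before the primary results are seen, replace the fixed Bonferroni rule with Holm's step-down at overall two-sided 5%: the smaller of the two primary p-values is compared with 0.025 and, only if it is significant, the other with 0.05. Leave Sample size justification as it is; its 0.025 remains the first-step level. If the primary results have already been seen, keep Bonferroni.

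The cost is one sentence and less simple intervals. An endpoint rejected at the second step with p between 0.025 and 0.05 has a 97.5% interval that includes no difference, so the report should state which level each interval uses.

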## Discussion

The purpose of our study is to proof the feasibility and effectiveness of a multilevel intervention in preschool children aiming to increase physical activity and motor skills. The effects on adiposity, media time, blood pressure, infections and accidents will also be assessed.

We believe that the involvement of the kindergarten teachers in the activity programme will not only translate in an effective intervention tailored to the need of each individual facility, but also in a continuation of the programme after the end of the formal intervention period. Furthermore, it is likely that the empowerment achieved by this study in the kindergarten teachers might also facilitate the transfer to other kindergartens since an involvement of the intervention kindergartens in the training of other teachers is planned. If the study can show feasibility and effectiveness of the intervention, the nationwide transfer of the project will be realised in cooperation with a health insurance company (BARMER GEK).
